## Introduction

### Background and rationale {6a}

Annually, there are approximately 12.8 million adults over the age of 65 hospitalized in the USA [1]. Hospitalization contributes to functional decline of older patients [2–6]. Inpatients spend as much as 95% of their time in bed, [7] and bed rest is associated with increased risk of complications such as falls, venous thromboembolism, skin breakdown, and hospital-acquired pneumonia [8, 9]. Such adverse events delay eventual recovery and increase costs as patients spend time in both acute and post-acute (e.g., skilled nursing and inpatient rehabilitation facility) care.

Frequent in-hospital physical therapy may contribute to improved function and discharge home, [10–12] but physical therapists primarily treat patients with significant functional impairments. They should not be the first-line clinicians for providing general mobility interventions (i.e., any activity out of bed, including ambulation) [13, 14]. Evidence is growing that general mobility interventions can be facilitated by non-therapists and may mitigate adverse events and improve patients’ functional status [9, 15–26]. The studies for this evidence base, however, are mostly observational and the effects are mixed. One randomized controlled trial has shown promise, but the effect on patients’ outcomes was assessed after hospitalization [27]. In each, interventions were facilitated by a bedside nurse or a designated mobility technician. Nurses, however, have multiple competing demands that often take precedence, [28] a problem exacerbated by the COVID-19 pandemic and resulting nationwide nursing shortage [29–31]. Additionally, fall prevention strategies—which are a necessary priority for nurses—often limit mobility out of bed [32]. Primarily for these reasons, ambulation is missed approximately 75% of the time even when it is ordered by a physician [7, 33–35].

A mobility technician (MT), a clinical team member with the sole responsibility of helping patients to regularly complete general mobility interventions, may be a viable solution to these problems. However, this is not a typical role in hospitals. A lack of empirical evidence that a MT can improve outcomes makes it challenging for hospital administrators to justify the creation of MT positions since doing so would increase costs for the hospital. There is a need for non-observational studies that examine the effect of a MT on both in-hospital and post-hospital outcomes.

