### Eligibility criteria {10}

Medical (i.e., non-surgical) patients in the first 48 h of their admission will be identified by the MT, aided by an automatically generated daily report and collaboration with bedside nurses on the unit. This method increases the pragmatism of the study. Participants must meet all of these inclusion criteria upon review of the medical chart in the electronic health record:≥65 years of age.Inpatient admission status to a medical service.Complete history and physical examination on file in the electronic health record.Moderate activity impairment based upon a raw score of 16–20 on the Activity Measure for Post-Acute Care (AM-PAC) 6-Clicks basic mobility short form. The 6-Clicks tool is a valid and reliable measure of function for patients in the acute hospital [38, 39]. Scores in this range are consistent with a patient who requires only a little physical assistance to complete basic mobility tasks like getting out of bed and walking, suggesting they are safe to get out of bed with a MT, but at risk of functional decline without assisted ambulation.Insurance with traditional Medicare or Medicare Advantage. This will be required to determine post-hospitalization costs.

Exclusion criteria include:Significant language barrier that requires a translator, except at Baystate where Spanish speakers may enroll since Spanish language translators are readily available.Discharge planned within 24 h of screening.Surgical procedure planned.Diagnosed with unstable angina or other medical conditions precluding participation in exercise/ambulation.Permanent residence in a skilled nursing facility.Comfort care measures only.Active infection with SARS-CoV-2 or other pathogen requiring contact or droplet precautions.An order for bed rest that is clinically warranted due to safety concerns identified by a treating physician. Whether a bed rest order meets this criterion will be clarified by the MT with the nurse.Not previously enrolled in the study.

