### Methods for additional analyses (e.g., subgroup analyses) {20b}

We will conduct three sensitivity analyses to account for (1) missing outcomes data, (2) treatment heterogeneity by site, and (3) the dose-response curve in the intervention group.

To identify the patients most likely to benefit from ambulating with a MT, we will build models separately for each treatment arm to predict the outcome of at least 1-point increase in the SPPB (i.e., beyond the minimal clinically important difference). Using the predicted probabilities resulting from these models, we will develop a Classification and Regression Tree (CART) that should identify subsets of patients likely to benefit, not benefit, or be harmed by the treatment. For example, the analysis might show that female patients aged >75 years who have an initial 6-Clicks score between 16 and 18 have an estimated treatment benefit of being 22% more likely to achieve the 1-point increase in SPPB. Essentially the tree will form risk groups of patients with shared characteristics that should receive a similar care recommendation.

We will estimate the total cost of the episode of care including the index admission (from hospital cost accounting systems) and all non-medication costs for the 30 days following enrollment (from Medicare claims) for all patients. For the intervention group, we will add the personnel costs for the MTs (hourly wages plus benefits). Since cost data are skewed, our cost estimates will be transformed and then compared between groups using the *t*-test.

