## Discussion

In a 1947 issue of the British Medical Journal, Asher [63] advised against bed rest, writing: “Get people up and we may save our patients from an early grave.” Hirsch and colleagues [4] observed in 1990 that hospital-associated functional decline improved at a much slower rate than the acute illness. Such observations—now accumulated in multiple studies over more than 70 years—have led to labeling hospital-associated functional decline as an under-recognized epidemic [7] and identifying its role as part of the so-called post-hospital syndrome [64].

The primary objective of our study is to examine the extent to which ambulation interventions provided by an additional clinical team member—a MT—affects functional decline and other hospital-important outcomes (e.g., length of stay and discharge disposition) at costs that could be tenable for hospitals. Given current evidence, it is unclear if ambulation alone is enough to prevent the decline patients experience in the hospital. Further, we do not know how much ambulation may be required nor which patients benefit from ambulation, alone or in combination with other mobility interventions.

Appropriate exercise interventions in the hospital can, at the very least, attenuate functional decline. After cardiac surgery, ambulation facilitated by “ambulation orderlies” reduced functional decline and LOS [22, 37]. Kosse et al. [65] found in their systematic review that exercise interventions (provided by physical therapists or nurses) improved performance of physical function tests, contributed to fewer discharges to post-acute care facilities, and reduced hospital length of stay in a clinically heterogeneous sample of older adults. Similarly, in their single-center randomized controlled trial (*N*=370), Martinez-Velilla et al. [66] demonstrated that an individualized, multicomponent (resistance, balance, and basic mobility) exercise intervention in the hospital prevented functional decline and improved cognitive status.

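### The Aim 2 target counts only SPPB gains of at least 1 point, so effects confined to patients who would not gain (decline prevented or made worse) do not register

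*Protocol article*

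**What the plan says.** The section on additional analyses {20b} of the protocol article fixes the Aim 2 method in three steps.

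- Target: "we will build models separately for each treatment arm", each meant to "predict the outcome of at least 1-point increase in the SPPB (i.e., beyond the minimal clinically important difference".
- Output: a tree grown on the predicted probabilities, which should "identify subsets of patients likely to benefit, not benefit, or be harmed by the treatment". Patients in the same group are then to get a similar recommendation about care.
- Scale: in the worked example, a subgroup is said to "have an estimated treatment benefit of being 22% more likely to achieve the 1-point increase in SPPB". Benefit is thus a between-arm difference in the probability of a gain.

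Elsewhere the article presents decline as the problem. The background {6a} says "Hospitalization contributes to functional decline of older patients". The eligibility section {10} justifies the 6-Clicks range because such patients are "at risk of functional decline without assisted ambulation". The Discussion says of earlier work: "Appropriate exercise interventions in the hospital can, at the very least, attenuate functional decline". It also gives the study's main purpose as the effect on functional decline and other outcomes.

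The primary analysis {20a} compares the full SPPB change score between arms.

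**The concern.** The tree is meant to form three classes, but its target records only one direction of change. Every patient who does not gain a point is in the same category, whether stable or several points worse. A treatment effect that moves patients about within that category leaves the target as it was. Two such effects matter here: a decline that is prevented, which is central to the trial's rationale, and a worsening, which is what a harm class should detect.

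The Discussion plans a classification model for hospitals, possibly built into the electronic health record. A subgroup whose only benefit is avoided decline could be listed as not benefiting, and a subgroup in which non-gainers get worse could be listed the same way instead of as harmed. The issue is the outcome being modelled, not over-fitting of the tree.

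**Working it through.** **Inputs from Sample size {14}.** N = 3000, SD of SPPB change 2.7, MCID 0.54, two-sided alpha 0.05, 10% dropout, 20% non-compliance. The article gives no control-arm mean change, no subgroup size and no power figure for Aim 2. Those used below are assumptions, as are normality and, where stated, whole-point scoring.

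**The plan's own figure on this scale.** With 1350 per arm (1500 less 10%), the standard error is 2.7 × √(2/1350) = 0.104.
- Difference 0.54: Φ(0.54/0.104 − 1.96) = 99.9%.
- Effect diluted by 20% to 0.432: 98.6%.

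The stated power above 99% is reproduced to within about a point.

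**1. Effects confined to non-gainers.** Assume a usual-care mean of −0.5, SD 2.7, whole points.
- P(gain ≥ 1) = 1 − Φ((0.5 + 0.5)/2.7) = 35.6%
- P(loss ≥ 1) = Φ((−0.5 + 0.5)/2.7) = 50.0%
- P(no change) = 14.4%

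The mean differences in the first two rows come from a simulation of 2 million draws. The last two follow from 0.644 × fraction × 2, where 64.4% are non-gainers.

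| Treatment effect | Difference in mean change | P(loss ≥ 1), control to MT | P(gain ≥ 1), control to MT |
|---|---|---|---|
| 25% of declines become no change | +0.34 | 50% to 37.5% | 35.6% to 35.6% |
| 50% of declines become no change | +0.67 | 50% to 25% | 35.6% to 35.6% |
| 25% of non-gainers 2 points worse | −0.32 | 50% to 53.6% | 35.6% to 35.6% |
| 50% of non-gainers 2 points worse | −0.64 | 50% to 57.2% | 35.6% to 35.6% |

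The second and fourth rows exceed the MCID in size, and the Aim 2 contrast is zero in both.

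**2. Effects that shift everyone.** Whole points, SD 2.7.
- A benefit of 0.54 raises P(gain) by 5.7, 7.2, 7.7 and 7.9 percentage points at usual-care means of −2, −1, −0.5 and 0.
- A harmful shift of 0.54 lowers it by 6.4 points at mean −1 (28.9% to 22.5%) and by 7.6 points at mean 0 (42.7% to 35.0%, before rounding).

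Both are visible, even when the average patient declines.

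**3. Dependence on the usual-care course.** Take the same +1-point effect in two subgroups, with a continuous score and P(gain) = 1 − Φ((1 − mean)/2.7).
- Mean −2: 13.3% to 22.9%, a gain of 9.6 percentage points.
- Mean +0.5: 42.7% to 57.3%, a gain of 14.7 points before rounding.

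The tree could separate these subgroups although the effect in SPPB points is identical.

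**4. Precision.** Assume a subgroup of 300 per arm and a true shift of 0.54.
- Change score: standard error 2.7 × √(2/300) = 0.220, power Φ(0.54/0.220 − 1.96) = 69%.
- Gain of at least 1 point (whole points, usual-care means −2 to +1): power about 40% to 50%.

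**The case against.** Several stronger readings are tempting, and the document does not support them.

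- A reader might infer that harm cannot be seen and that the harmed class has no basis. Benefit and harm here are between-arm contrasts in P(gain), and a negative contrast is a valid sign of harm. Only worsening among patients who would not have gained is missed.
- A reader might infer that a declining subgroup will always be labelled as not benefiting. The labels attach to subsets, not to individual non-responders, and step 2 shows a positive contrast even at a usual-care mean of −2.
- A reader might infer that a gain target contradicts the trial's aims. The first aim {7} asks about improved mobility, the pilots {8} showed a small increase, and the futility rule {21b} is framed as failure to improve mobility. The eligibility text speaks of risk of decline, not of an expected mean loss, and the Discussion sentence on attenuation describes earlier exercise interventions.
- A reader might expect a far larger distortion. With an assumed within-subgroup SD of 1.5, the contrasts in step 3 become 6.8 and 26.1 points. With a common within-subgroup SD, that would need subgroup membership to explain about 69% of the variance (1 − 2.25/7.29), and nothing in the article supports this.

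A responder threshold above the MCID is also a recognised choice that clinicians can interpret, and falls are compared separately.

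All of this stands. It narrows the point but does not remove it: the target is still blind to changes below the gain threshold and still discards information. Nor is this a detail left to an analysis plan, since the article itself fixes the target.

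**Conclusion.** The point holds in a limited form. Between-arm differences confined to patients who would not gain leave the Aim 2 target unchanged; in the illustration, mean effects of +0.67 and −0.64 points both give a contrast of zero. Effects across the whole distribution do appear, with less precision (about 40% to 50% power against 69% in the assumed subgroup) and with a size that varies with the usual-care course (9.6 against 14.7 percentage points at SD 2.7).

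These figures rest on normal change scores and on assumed usual-care means and subgroup size. How far real effects would be confined to non-gainers is unknown, so the tables show what the target can miss, not what it will miss. The target is incomplete for a three-class aim rather than wrong, and the primary comparison, which uses the full change score, is untouched. This is a cheap improvement worth making before analysis.

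**What to change.** In the additional-analyses section {20b}:

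1. Model SPPB change as a continuous outcome in each arm.
2. Grow the tree on the predicted between-arm difference in mean change.
3. Interpret each subgroup's difference by its sign and by its size against the 0.54-point MCID.
4. Keep the 1-point gain as a display, within a three-level summary by arm: loss of at least 1 point, change within 1 point, gain of at least 1 point.

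This uses SPPB data already collected, puts Aim 2 on the same scale as the primary outcome, and changes only the analysis wording. The cost is a slightly less direct headline than a percentage more likely to gain a point, and the three-level display supplies that figure.

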## Objectives {7}

AMBULATE has three primary aims: first, to determine whether an ambulation program delivered by a MT improves patients’ mobility status at hospital discharge. As related objectives, we will examine if the intervention decreases hospital-related complications, including falls, venous thromboembolism, pressure ulcers, and hospital-acquired pneumonia; if it impacts discharge disposition (i.e., home vs. post-acute care facility); and if mobility improvement is sustained after hospital discharge. Second, we will use predictive modeling to identify which patients are more likely to benefit from this intervention. Third, we will assess the impact of the intervention on overall costs associated with the episode of care, including inpatient costs and medical costs following discharge.

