## Methods: participants, interventions, and outcomes

### Study setting {9}

The study will be conducted in five hospitals—four in the Cleveland Clinic Health System (Northeast Ohio, USA) and Baystate Medical Center (Springfield, MA, USA). Each hospital will employ 2 MTs to ensure that one is always available to provide the intervention.

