### Sample size {14}

A sample size of 3000 has >99% power to detect a difference in SPPB change as small as 0.54 points (the MCID) between the two groups at a two-sided alpha of 0.05, assuming a common SD of 2.7 for the SPPB change, 20% non-compliance, 10% dropouts, and an interim analysis. The estimates for MCID and SD are based on observation of older acute care medical patients [43, 44]. Using these same assumptions, the power is still 92% for detecting a smaller difference of 0.35. Therefore, we expect ample statistical power for analyzing the primary outcome. The main reason for selecting this sample size is to ensure that the analyses of important secondary outcomes are not underpowered. The most important of these is discharge disposition, because even a small absolute difference in the number of patients discharged to home, as opposed to a skilled nursing facility, is clinically important. We will be able to detect a 7% difference in discharge to home vs. SNF with 98% power.

For other binary secondary outcomes (a combination of venous thromboembolism, pneumonia and falls, 30-day mortality, or 30-day readmission), the study will have 85% power to detect a 33% reduction assuming an 8% rate in the control group. Because these outcomes are not contingent on patient cooperation, we anticipate no dropouts. For secondary continuous outcomes such as length of stay, assuming 20% non-compliance rate, the power to detect a 4-h difference (0.167 days) is 95%.

Regarding the cost analysis, there is no accepted way of doing a power calculation. However, we tried adding $300 (an approximation of the cost of the intervention) to the costs of each of 1500 patients drawn randomly from a sample of 3000 Cleveland Clinic medical inpatients over the age of 65 with an AM-PAC 6-Clicks score between 16 and 20. We then performed a *t*-test on the log-transformed costs, as described in the economic analysis section, and we were able to detect the increase with a p-value of 0.03, indicating that should the intervention increase costs by an amount equal to the cost of the intervention, we should be able to identify it. Similarly, if the intervention decreases total costs by $300 or more (not including the costs of the intervention), we should have sufficient power to detect it.

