## Assignment of interventions: allocation

### Sequence generation {16a}

Randomization will be done using a computerized system. A block randomization scheme with a size of 4 will be used to ensure approximately equal numbers of patients per group. Allocation will be stratified within units within hospitals.

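### The cost comparison uses an unadjusted t-test although allocation is stratified by unit within hospital, so its standard error is overstated by an amount the documents do not let us fix

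*Protocol article*

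**What the plan says.** Under Objectives {7} the article states that "AMBULATE has three primary aims"; the third is that "we will assess the impact of the intervention on overall costs associated with the episode of care".

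Under Study setting {9}, "The study will be conducted in five hospitals": four in one health system and one in another. Under Methods for additional analyses {20b}, the index-admission cost is taken "from hospital cost accounting systems", Medicare claims supply the non-medication costs up to 30 days after enrolment, and mobility technician personnel cost is added in the intervention arm. Then "our cost estimates will be transformed and then compared between groups using the *t*-test". Sample size {14} also describes a t-test on log-transformed costs, so the method is stated twice.

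Under Sequence generation {16a}, blocks of 4 are used and "Allocation will be stratified within units within hospitals".

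The support for the cost aim in Sample size {14} is one exercise. It added $300 to the costs of "1500 patients drawn randomly from a sample of 3000 Cleveland Clinic medical inpatients", ran the t-test on log cost and obtained p = 0.03.

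No site or unit term is given for cost. Site is a fixed effect only in the fallback mixed model for the SPPB (Statistical methods {20a}). The by-site sensitivity analysis in {20b} concerns treatment heterogeneity. The Discussion promises adjustment only if covariates prove unbalanced.

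**The concern.** Hospital cost levels can differ for reasons unrelated to treatment: accounting method, wages, case mix, unit type. Blocking within unit within hospital spreads these differences almost evenly over the arms, so they add almost nothing to the true sampling error of the treatment difference. A two-sample t-test does not know this. It estimates its error from the total spread of cost, including the spread between strata, and so reports a standard error larger than the actual one.

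At stake is how precisely the cost aim can be reported. Too wide an interval and too conservative a test reduce the chance of recognising a cost increase or saving of about $300, the amount the plan itself uses. The conditional adjustment in the Discussion is unlikely to help, because stratification makes imbalance by hospital improbable and the condition would rarely be met.

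**Working it through.** **Inputs.** From the article: 1500 per arm, p = 0.03 for a $300 increase, blocks of 4 within unit within hospital, five hospitals. Two-sided alpha of 0.05 is stated for the SPPB and assumed here for cost. The share ρ of log-cost variance lying between strata is not given anywhere; it is an assumption, shown from 2% to 30%.

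**The plan's own figure.** The p = 0.03 cannot be reproduced, because no cost mean or SD is given. It can be inverted. Two-sided p = 0.03 corresponds to z = 2.170. With 1500 per arm the implied standardised effect is 2.170 × √(2/1500) = 0.079 SD. Power at that effect is Φ(2.170 − 1.960) = Φ(0.210) = 58%.

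**Formulas.** A stratum term removes the share ρ from the error variance:
- SE ratio, adjusted to unadjusted: √(1−ρ)
- actual type I error of the unadjusted test under stratified allocation: 2 × [1 − Φ(1.96/√(1−ρ))]
- actual power of the unadjusted test under stratified allocation: Φ((2.170 − 1.96)/√(1−ρ))
- power of the adjusted test: Φ(2.170/√(1−ρ) − 1.96)

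The third line matters. The unadjusted test's true sampling error is itself below its reported one, so its power is slightly above 58% and the gain must be measured from there.

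| ρ (assumed) | SE ratio | SE reduction | Unadjusted type I error | Unadjusted power | Adjusted power | Gain, points |
|---|---|---|---|---|---|---|
| 2% | 0.990 | 1.0% | 4.8% | 58.4% | 59.2% | about 1 |
| 5% | 0.975 | 2.5% | 4.4% | 58.5% | 60.5% | about 2 |
| 10% | 0.949 | 5.1% | 3.9% | 58.8% | 62.8% | about 4 |
| 20% | 0.894 | 10.6% | 2.8% | 59.3% | 67.9% | about 9 |
| 30% | 0.837 | 16.3% | 1.9% | 59.9% | 73.7% | about 14 |

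A gain of 5 points needs a share of about 12%.

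**Simulation check** (5 hospitals × 600 patients, blocks of 4, 3000 runs per scenario, hospital term against pooled t-test). At ρ = 10% the mean reported SE was 0.0365 SD unadjusted and 0.0346 SD adjusted, with type I error 4.0% and 5.0% and power 58.7% and 62.9%. At ρ = 20% the SE was 0.0365 and 0.0327, type I error 2.5% and 5.0%, and power 62.1% and 70.1%. Both simulated powers at 20% lie 2 to 3 points above the formula, but the gain of 8 points is close to the formula's 9. In this balanced layout the spread of the treatment estimate over runs was the same with and without the hospital term; only the reported error differed.

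**The case against.** The strongest objection is that the size is unknown. The documents give no cost SD, no between-hospital difference and no variance share. Four of the five hospitals share a health system. If recruitment is equal, as the target of 200 patients per year per hospital implies, one fifth of patients come from the other system. For a difference between the two systems alone to make up 10% of the variance, it would have to be √(0.10/0.90/(0.2 × 0.8)) = 0.83 within-system SD of log cost. Nothing in the article shows this. The objection stands as a limit on size, although differences between units and between hospitals of the same system also count towards the share.

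Second, the 58% anchor is weak. It rests on one p-value from one random draw. Chance alone gives z an SD of 1, so the underlying z could lie between 2.17 − 1.96 = 0.21 and 2.17 + 1.96 = 4.13, which is power of about 4% to 98.5%. The exercise also used Cleveland Clinic patients only, so it lacks the between-system variance that the trial's t-test will contain. Using its z as the pooled-test value is therefore an approximation. This stands: the power figures are illustrative. The SE and type I error figures do not depend on this anchor.

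Third, the article condenses a fuller plan. Sample size {14} points to an economic analysis section that the article does not contain under that name, and supporting models may be specified there. But the article names the t-test for cost twice, so this is a stated choice and not an omission.

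A reader might also infer that the cost comparison is biased, that false positives are inflated, or that cost is the most weakly powered of the three aims. The documents support none of these. Randomisation keeps the estimate unbiased, the error in the test is towards caution, and no power figure is given for the prediction aim with which cost could be compared.

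**Conclusion.** The point holds as one of precision and conservativeness, of uncertain size. The unadjusted t-test ignores the stratified design, and nothing else in the article corrects this for cost. The loss is negligible if strata explain 2-5% of log-cost variance and becomes material from roughly 10-12% upward. Across the assumed range of 2% to 30% the reported SE could be cut by 1% to 16%. These figures assume near-complete balance within strata, two-sided alpha of 0.05 and a constant treatment effect on the transformed scale. They do not show that the cost aim will fail or that its loss of power is large. The change is worth making because it costs almost nothing and brings the test back to its stated error rate.

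**What to change.** In Methods for additional analyses {20b}, replace the t-test for cost with a linear model of cost, on the planned transformed scale, on treatment with the randomisation strata as fixed effects. Include hospital at least, and unit within hospital where numbers allow, with small units pooled within their hospital, since the number of units is not stated. Baseline 6-Clicks score may be added as an optional covariate; eligibility confines it to 16-20 and its gain has not been quantified. Report the adjusted treatment difference with its confidence interval.

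The cost is one line of wording, settled before unblinded cost data are seen. Strata are known at randomisation and 6-Clicks is recorded at entry, so no new data, patients or staff are needed.
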